## Background

Hilar cholangiocarcinoma is one of the most common bile duct cancers, accounting for 60–70% of extrahepatic cholangiocarcinomas. Surgical resection remains the mainstay of potentially curative treatment for hilar cholangiocarcinoma. However, the probability of radical curative resection is low, and the prognosis is insufficient [1–3].

The incidence of lymph node metastases is high on the presentation or exploratory laparotomy. As the prognosis of patients with nodal metastases is significantly worse, the American Joint Committee on Cancer (AJCC) has modified the staging of lymph nodes invasion (N) several times during the last decade. However, concerning lymphatic dissection, there are still many disputes [1, 4, 5], and currently, no consensus has been reached on the preferred method of lymphadenectomy in patients with hilar cholangiocarcinoma. The incidence of complications after extended and regional lymphadenectomy has only been assessed in small retrospective series.

We hypothesize that extended lymph node dissection (8a/p, 9, 12a/b/c/h/p, 13a, 14, 16) might improve the prognosis of the patients without elevating the major complication rate. Therefore, the primary objective is to determine the overall survival (OS) rate for the two approaches with the secondary endpoint of perioperative mortality, postoperative complications, and disease-free survival (DFS). This study will explore the prognostic benefits and safety of extended lymphadenectomy for hilar cholangiocarcinoma.

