### Procedure

The routine approach for hilar cholangiocarcinoma surgery is based on the National Comprehensive Cancer Network (NCCN) Guidelines Insights: Version 2.2019 Hepatobiliary Cancers [13]. The surgical procedures consist of (extended) hemi-hepatectomy and complete lymphadenectomy of the hepatoduodenal ligament. The (extended) hemi-hepatectomy contains en bloc excision of the liver hilum, extrahepatic bile ducts, and caudate lobe. Portal vein excision and reconstruction would be performed when the tumor infiltrates into the portal vein bifurcation. In this study, we will utilize the lymph node classification system by the Liver Cancer Study Group of Japan (Additional file 1: Figure S1) [14]. Patients in the regional lymph node dissection group will receive radical resection and numbers 8a/p, 12a/b/c/h/p, 13a lymph nodes dissection. In contrast, patients in the extended lymph node dissection group will receive radical resection and numbers 8a/p, 9, 12a/b/c/h/p, 13a, 14, 16 lymph nodes dissection. Experienced surgeons in each center will be educated in a standardized surgical approach, especially the surgical procedures and lymph node harvest procedures. There will be digital recording (video and photography) for each operation, which will be evaluated by third-party surgical experts, namely the data monitoring committee (DMC). The intraoperative evaluation, safety assessment, and tumor specimens will be evaluated by the surgical teams who perform the surgery as well as pathologists.

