### Blinding

Concerning random allocation, a sealed envelope will be issued to the surgeon before the operation by a project secretary. Normally there are two secretaries who are recruited for the clinical trial data management who are not involved in the operation. Then the surgeon unpacks the envelope and performs the operation according to the allocation in the envelope. The patients, outcome assessors, pathologists, and data analysts will not know the grouping information.

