### Observation indices

The primary endpoint will be the 5-year OS rate. The secondary efficacy index includes the primary complication (Clavien-Dindo grades > II) within 30 days postoperatively, perioperative mortality, 6-month OS and DFS, 1-year OS and DFS, 3-year OS and DFS, and 5-year DFS. Cancer-specific survival is determined at the time of cholangiocarcinoma-related death. Disease-free survival is the time to any recurrence. The efficacy evaluation is based on the postoperative pathology: if the postoperative pathological margin is negative and LN ≥ 6, the operation is considered to have achieved the desired purpose. The safety index includes vital signs, adverse events, and clinical laboratory parameters (blood routine, urine routine, myocardial enzymes, coagulation, blood biochemistry, electrocardiogram, cardiac ultrasound), as well as early withdrawal (Fig. 2).

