The principal analysis consists of an intention-to-treat comparison of the major complications in both groups, using a Mann-Whitney *U* test for ordered categorical data with a two-sided 0.05 significance level. The proportion of patients with any severe operation-related complication will also be expressed in terms of relative risk (RR) and 95% confidence interval (CI). Categorical variables are evaluated using Pearson’s χ^2^ test or Fisher’s exact test.

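### The principal test for major complications is a two-sided difference test on ordered categories, which cannot by itself show that the Clavien-Dindo > II rate is not raised; who grades complications also needs reconciling

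*Protocol article*

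**What the plan says.** **Hypothesis.** The Background section proposes that extended dissection "might improve the prognosis of the patients without elevating the major complication rate".

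**Endpoint.** Observation indices lists "the primary complication (Clavien-Dindo grades > II) within 30 days postoperatively" among the secondary indices. The Statistical analysis section repeats the same cut at grade II.

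**Analysis.** The Statistical analysis section states: "The principal analysis consists of an intention-to-treat comparison of the major complications in both groups". The method is a Mann-Whitney U "test for ordered categorical data with a two-sided 0.05 significance level". Overall survival is the primary endpoint, so I read this as the principal analysis of complications. The next sentence adds a relative risk with 95% confidence interval for the proportion with any severe operation-related complication. No largest acceptable increase is attached to either result.

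**Assessor.** Under Procedure: "The intraoperative evaluation, safety assessment, and tumor specimens will be evaluated by the surgical teams who perform the surgery as well as pathologists". Under Blinding, the surgeon opens the allocation envelope, yet: "The patients, outcome assessors, pathologists, and data analysts will not know the grouping information". The Follow-up section schedules a complication evaluation at 30 days and names no assessor.

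**The concern.** The safety half of the hypothesis claims no increase in a rate. The stated principal analysis asks whether two distributions of ordered categories differ. There are two mismatches.

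- **Direction of proof.** Failing to reject equality is not evidence of equality. If power against an increase that matters is modest, a p-value above 0.05 is a likely result even when the increase is real.
- **Quantity.** The endpoint is a proportion above a cut. A rank test on several categories responds to shifts anywhere on the scale, including shifts below the cut if those grades are ranked.

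There is also a separate conflict about who judges safety. Complication grading involves judgement, so it matters whether the grader knows the arm.

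At stake is whether the trial can support its statement that extended dissection does not raise major morbidity. The overall survival comparison is not affected.

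**Working it through.** **Inputs**

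- Number per arm: the Design section gives 330 before loss and 10% loss. 330 / (1 − 0.10) = 366.7, so 367, as stated. I use 367 because the complication comparison is by intention to treat, all randomised patients are in the full analysis set, and the endpoint is at 30 days. The article gives no sample-size figure for complications to reproduce.
- Significance level: two-sided 0.05 (Statistical analysis).
- Major complication rate: not given per arm. The 63% in the Discussion is from cited literature and is not restricted to major grades. **Assumed** regional-arm rates: 10%, 20%, 30%, 40%.
- Rise to be detected: **assumed** 5 or 10 percentage points.

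**Step 1. Power of a difference test.** The two-proportion test stands in for the planned test:

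power = Φ{ [d − 1.96 √(2p̄(1−p̄)/n)] / √([p₁(1−p₁)+p₂(1−p₂)]/n) }

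Example, 20% vs 25%: p̄ = 0.225; √(2 × 0.225 × 0.775 / 367) = 0.03083; √((0.16 + 0.1875)/367) = 0.03077. Then (0.05 − 1.96 × 0.03083)/0.03077 = −0.339, and Φ(−0.339) = 0.367.

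**Step 2. What the interval could say if the observed rates were equal.** Upper limit of the risk difference = 1.96 √(2p(1−p)/n). Upper limit of the relative risk = exp{1.96 √(2(1−p)/(np))}.

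| Assumed regional rate | Power, +5 points | Power, +10 points | Upper limit, difference | Upper limit, RR |
|---|---|---|---|---|
| 10% | 54% | 97% | +4.3 points | 1.54 |
| 20% | 37% | 88% | +5.8 points | 1.34 |
| 30% | 30% | 81% | +6.6 points | 1.25 |
| 40% | 28% | 78% | +7.1 points | 1.19 |

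With a true 5-point rise, 46-72% of such trials (1 minus power) would report no significant difference.

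**Step 3. What the rank test measures, if grades I-II are ranked.** The Mann-Whitney test concerns θ = P(extended worse) + ½P(tie), with θ = 0.5 for no difference. Take three categories (none, I-II, > II) and an **assumed** regional arm of 0.4 / 0.4 / 0.2.

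- Extended 0.4 / 0.3 / 0.3 (major rate up 10 points): P(worse) = 0.3×0.4 + 0.3×0.8 = 0.36; P(tie) = 0.16 + 0.12 + 0.06 = 0.34; θ = 0.36 + 0.17 = 0.53.
- Extended 0.3 / 0.5 / 0.2 (major rate unchanged, minor up 10 points): P(worse) = 0.5×0.4 + 0.2×0.8 = 0.36; P(tie) = 0.12 + 0.20 + 0.04 = 0.36; θ = 0.36 + 0.18 = 0.54.

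On this scale the second case, with no rise in major complications, is slightly further from 0.5 than the first, where the major rate goes from 20% to 30%. For that same first case, a comparison of the > II proportions has 88% power (Step 1).

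**Step 4. What a margin would require.** With equal true rates and one-sided 0.025, power = Φ(m / √(2p(1−p)/n) − 1.96) at n = 367. Number per arm for 80% power = (1.96 + 0.842)² × 2p(1−p)/m². Both margins are illustrative.

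| Rate | Power, m = 5 | Power, m = 10 | n per arm, m = 5 | n per arm, m = 10 |
|---|---|---|---|---|
| 10% | 62% | 99.5% | 566 | 142 |
| 20% | 39% | 92% | 1005 | 252 |
| 30% | 31% | 84% | 1319 | 330 |
| 40% | 28% | 79% | 1507 | 377 |

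**Step 5. The assessor.** Procedure gives safety assessment to the team that operates. Blinding has the surgeon in that team open the envelope. Observation indices includes adverse events in the safety index. Blinding also says outcome assessors do not know the group. These statements agree only if the grader of 30-day complications is someone outside the operating team, and no section says so.

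**The case against.** **The binary quantity is already planned.** A reader might infer that the plan as a whole cannot support the safety claim. The documents do not go that far: the relative risk with 95% confidence interval stands directly after the rank test and is the right kind of quantity. What remains is that it is an addition to the principal test and carries no limit, so it gives no decision rule.

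**A margin may be in the full protocol or analysis plan.** That is fair, and the absence of a margin alone would be no finding. The point is that the article itself fixes the principal test, its sidedness and its role, and that rule does not address the article's own hypothesis. It is also true that complications are secondary and the hypothesis is hedged.

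**Grades I-II may not enter the ranking.** A reader might infer that mild events dominate the test. The text applies it to major complications and does not list the categories; they could be none, III, IV and V. Step 3 is therefore conditional. The Discussion's remark that mild events are commonest summarises cited studies, not this trial.

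**Grading by the operating team is not stated.** A reader might infer it from "safety assessment, and tumor specimens will be evaluated by the surgical teams who perform the surgery as well as pathologists". However, Observation indices puts Clavien-Dindo > II under the secondary efficacy index, not the safety index, so the team could record safety data while blinded assessors judge outcomes. Adverse events overlap with complications, so the sections still need reconciling.

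**No direction of bias follows.** A reader might suppose that these features favour a finding of no difference. Unblinded grading can err either way, and more mild events after extended dissection would push an all-grade rank test towards a difference. Nor did the surgeons choose the dissection; it is randomised.

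**Conclusion.** The point holds in a limited form. The stated principal test cannot by itself establish that major complications are not elevated: at 367 per arm its approximate power against a true 5-point rise is 28-54%, so a non-significant result would be common despite a real rise. The range rests on assumed regional rates of 10-40%, an assumed 5-point rise, and a two-proportion approximation to the rank test. Against a 10-point rise, power is 78-97%, so the weakness concerns moderate increases. The mismatch between an ordinal test and a binary endpoint is certain in form; its effect depends on which grades are ranked. The conflict over blinding is an ambiguity to be resolved and is not proof of unblinded grading. The change should be made, because half of the stated hypothesis depends on it; the primary survival analysis does not.

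**What to change.** 1. **Statistical analysis.** Base the safety conclusion on the proportion with Clavien-Dindo > II within 30 days: risk difference and the already planned relative risk, each with a two-sided 95% confidence interval. Keep the Mann-Whitney test as supportive and state which grades it ranks.
2. **Decision rule.** Conclude that the rate is not elevated only if the upper confidence limit lies below a margin fixed, with its justification, before unblinding. If no margin can be justified, limit the claim to describing the difference and its interval, and do not infer absence of an increase from p > 0.05. The planned size is reasonable for a margin of about 10 points (79-99.5% power at equal true rates) and weak for 5 points (28-62%); these margins are illustrations only.
3. **Procedure, Blinding and Follow-up.** Reconcile the three sections and state that the blinded outcome assessors already named assign the Clavien-Dindo grade.

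Cost: changes of wording, one margin to agree, and routing existing records to assessors the protocol already has. No extra patients or visits are needed. The downside is that the safety claim becomes harder to make.

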## Discussion

The main factors that affect the prognosis include cellular differentiation, perineural infiltration, and lymphatic and microvascular infiltration. Lymph node metastasis is an important factor leading to poor prognosis. It is reported that the rate of lymph node metastasis in hilar cholangiocarcinoma is 20–50%. When cholangiocarcinoma has already spread to the lymph node, the 5-year survival rate declines to 5% [1–3]. At present, lymphatic dissection for hilar cholangiocarcinoma remains controversial. In the seventh edition of the AJCC hilar cholangiocarcinoma guidelines, “N” staging was based on the lymph node infiltrating range, suggesting that the area of lymph node metastasis is an important parameter for hilar cholangiocarcinoma prognosis [4]. Several other studies confirmed that the survival rate of hilar cholangiocarcinoma patients with para-aortic lymph node metastasis (N2 in the seventh phase of AJCC) was significantly shorter than that for patients with regional metastasis (N1 in the seventh phase of the AJCC). The 5-year survival rate was only 0–12% [1]. In contrast, other researchers found that patients with regional or para-aortic lymph node metastasis have similar survival rates. This contradiction provokes more clinical research to explore the correlation between lymph node status and long-term outcome. The eighth edition of the AJCC staging system redefines the “N” staging based on the number of lymph node metastases. It reflects the prognostic value of the positive lymph nodes number and leads to higher demands for the dissection range of lymph nodes. Further studies are needed to investigate the sufficient number of lymph nodes’ dissection in order to harvest an accurate number of positive lymph nodes.

Whether the extended lymph node dissection could improve the prognosis of patients with hilar cholangiocarcinoma is yet unknown. The elevated comorbidity rate induced by extended dissection has always been a major concern for hepatobiliary surgeons. Hakeem et al. found that the 3-year and 5-year OS for regional lymphadenectomy were 41% and 31%, and the 3-year and 5-year OS for extended lymphadenectomy were 26% and 12% [10]. There was no significant difference in median OS and DFS between the two groups, suggesting no prognosis benefit in extended lymphadenectomy. Kitagawa et al. showed that the OS of patients who received regional lymphadenectomy plus para-aortic lymph node dissection was significantly better than that for those who only received regional lymphadenectomy [1]. The number of positive lymph nodes exceeding 20% was independent prognostic factor [15]. However, the complication rate for the former group was 63%, which was slightly higher than the rate for the regional lymphadenectomy group [16–18]. The in-depth analysis showed that the most common complications were pleural fluid and mild wound infections (Clavien-Dindo grades I–II) rather than complications such as lymphatic leakage, hemorrhage, and liver failure [19, 20]. In the preliminary study in our center, the perioperative mortality did not increase as other literature reported. Thus, the extended lymphadenectomy for hilar cholangiocarcinoma patients might be safe and feasible for a qualified hepatobiliary surgery center.

### Trial status

The protocol version number is RELAY-HC Ver5.0, which was registered on 15 April 2018 (ChiCTR1800015688). Recruitment began on 30 July 2018, and the approximate date when recruitment will be completed is 30 July 2023.

## Data Availability

Not applicable.

## Abbreviations

DFS: Disease-free survival
OS: Overall survival
